## Abstract

**Background:**

Peers are an important determinant of health and well-being during late adolescence; however, there is limited quantitative research examining peer influence. Previous peer network research with adolescents faced methodological limitations and difficulties recruiting young people.

**Objective:**

This study aims to determine whether a web-based peer network survey is effective at recruiting adolescent peer networks by comparing 2 strategies for reimbursement.

**Methods:**

This study will use a 2-group randomized trial design to test the effectiveness of reimbursements for peer referral in a web-based cross-sectional peer network survey. Young people aged 16-18 years recruited through Instagram, Snapchat, and a survey panel will be randomized to receive either scaled group reimbursement (the experimental group) or fixed individual reimbursement (the control group). All participants will receive a reimbursement of Aus $5 (US $3.70) for their own survey completion. In the experimental group (scaled group reimbursement), all participants within a peer network will receive an additional Aus $5 (US $3.70) voucher for each referred participant who completes the study, up to a maximum total value of Aus $30 (US $22.20) per participant. In the control group (fixed individual reimbursement), participants will only be reimbursed for their own survey completion. Participants’ peer networks are assessed during the survey by asking about their close friends. A unique survey link will be generated to share with the participant’s nominated friends for the recruitment of secondary participants. Outcomes are the proportion of a participant’s peer network and the number of referred peers who complete the survey. The required sample size is 306 primary participants. Using a multilevel logistic regression model, we will assess the effect of the reimbursement intervention on the proportion of primary participants’ close friends who complete the survey. The secondary aim is to determine participant characteristics that are associated with successfully recruiting close friends. Young people aged 16-18 years were involved in the development of the study design through focus groups and interviews (n=26).

**Results:**

Participant recruitment commenced in 2022.

**Conclusions:**

A longitudinal web-based social network study could provide important data on how social networks and their influence change over time. This trial aims to determine whether scaled group reimbursement can increase the number of peers referred. The outcomes of this trial will improve the recruitment of young people to web-based network studies of sensitive health issues.

**International Registered Report Identifier (IRRID):**

DERR1-10.2196/44813

## Introduction

### Background

Late adolescence is an important time in health and social development when many potentially modifiable health risks arise. This period often includes the exploration and initiation of behaviors including sexual activity, alcohol and other drug use, and the emergence of mental health problems [1]. Peer relationships are one of many interrelated determinants of health during adolescence [1]. For instance, adolescents with peers who engage in tobacco, alcohol, and cannabis use are more likely to initiate these behaviors themselves [2,3]. Despite the acceptance of peers as an important determinant of health, there is little recent quantitative research examining the influence of adolescents’ peer networks compared to research focused on the individual. Furthermore, the social environment that adolescents live in is constantly evolving, with more interactions taking place on the internet than in previous generations [4]. There is therefore a need for updated research about the influence of peers in the current context that leverages these new interactions and social connections.

Social network theory is an approach used to understand the influence of adolescents’ peers, among other things [5]. In the context of adolescent health behaviors, social network research involves the collection and analysis of information about relationships between individuals and their health behaviors [6]. Research seeks to understand the influence of a peer network and the mechanisms of this influence (eg, social pressure, communication of attitudes and norms, and social support) [6]. Understanding peer influence and its mechanisms can be used to design health interventions that leverage the strengths of adolescents’ social networks [7]. The majority of prior social network studies on adolescents have recruited participants from schools, with the “network” cast as entire classes or schools [3]. This recruitment setting produces high response rates and high ascertainment of contacts and links. It also has the potential for demographic diversity within the sample (particularly if several different schools were selected for the study). However, many longitudinal studies of this type were designed with relatively short follow-up periods (eg, 1-2 years) due to students changing classes and leaving school [8-10]. Studying a whole network (eg, an entire school or class) also limits the generalizability of findings to the wider adolescent population. As the network boundary is restricted, respondents are commonly limited to nominating friends from a directory within their class or their school year [11,12]. Alternative recruitment settings in social network research are community or health organizations. These settings were used by studies that sought specific subgroups (eg, youth experiencing homelessness or those with a specific health condition) and where recruitment staff had pre-established relationships with the participants [13,14]. However, studies recruiting from these settings reported difficulties reaching the desired sample sizes at sufficient speed [15,16]. Moreover, analyses of peer influence and sociometry in these studies were limited to egocentric data, meaning that primary participants report on the characteristics and behaviors of their friends, which limits the accuracy and reliability of behavioral reports [14].

Conducting social network research on peer groups using web-based techniques could overcome some of these disadvantages and has the potential to be used in longitudinal studies for the ongoing collection of information about people’s social networks beyond school. More broadly, web-based mechanisms are increasingly being used to recruit young people, as researchers have found web-based studies can effectively reach many young people, including those in more marginalized groups such as young people who identify as lesbian, gay, bisexual, transgender, queer, asexual, or other (LGBTQA+) [17,18]. Web-based questionnaires also provide greater privacy during completion than in person- or school-administered questionnaires, which is particularly important for sensitive topics such as sexual health and substance use [19]. To our knowledge, there are no social network studies with adolescents conducted entirely on the internet, but web-based cross-sectional, individual-level surveys have used social media recruitment, specifically Facebook, to recruit young people [17,20,21]. Social media platforms rapidly emerge, update, and outdate, resulting in frequent changes to their popularity and hence their usefulness as recruitment sites.

Web-based respondent-driven sampling (webRDS) offers a model for how we could recruit adolescents’ peer networks. Like traditional respondent-driven sampling (RDS), webRDS involves primary participants who are incentivized to recruit a specific number of peers into the study by offering a monetary reimbursement per recruited peer [22]. Studies using webRDS have either recruited the primary participants in person through study administrators [22,23] or used targeted Facebook advertising and phone screening to enroll primary participants [24]. Referral of secondary participants has been facilitated using emails [22,24] or private messages primarily via Facebook [23,24]. Reported benefits of using webRDS were that it was quicker, cheaper, and overcame barriers related to participants distributing physical coupons compared to RDS [23]. Potential limitations and considerations of webRDS include differences in participant demographics and risk profiles between recruitment using RDS and webRDS [23]. Fraudulent or duplicate cases were identified as a problem due to some participants trying to increase their reimbursement by creating false email addresses to artificially increase their number of referrals [24]. The reimbursements offered for survey completion and friend referral varied between each study, and the impact of the reimbursement was not tested. Therefore, the extent to which a reimbursement affects the recruitment of peers remains an important practical question that impacts the cost and feasibility of conducting a web-based social network study.

### Rationale

Our study will address gaps identified in previous research by determining whether a web-based approach is effective in recruiting adolescent peer networks. We will also address how different reimbursement models impact recruitment. In group 1 (experimental group: scaled group reimbursement), all participants within a peer network will receive an additional Aus $5 (US $3.70) voucher for each referred participant who completes the study, up to a maximum total value of Aus $30 (US $22.20) per participant. In group 2 (control group: fixed individual reimbursement), participants will only be reimbursed for their own survey completion.

If a web-based social network study proves feasible, this method has the potential to overcome barriers related to conducting longitudinal network research and use this web-based approach to better examine how social networks and their influence change over time. Identifying the characteristics associated with successful peer network recruitment would enable us to determine whether adolescents with certain key demographics or at-risk groups are more or less likely to refer their peers. By identifying these groups, we can gather further feedback and tailor the study methods in the future so that these social networks may be better captured.

### Aims and Research Questions

The primary aim of this study is to compare the effectiveness of 2 different financial reimbursement strategies for recruiting young people into a web-based peer network study. This will be explored through the following research questions:

Does a scaled group financial reimbursement for peer referral increase the proportion of an individual’s close friend network that completes the survey compared to having no peer referral reimbursement?Does a scaled group financial reimbursement for peer referral increase the number of close friends per participant who complete the survey compared to having no peer referral reimbursement?

We hypothesize that a scaled group financial reimbursement for peer referral will result in a significantly higher proportion of participants’ close friend networks and a significantly higher number of close friends per participant who complete the survey, compared to a fixed reimbursement rate for individuals.

The secondary aim is to determine what demographic and behavioral factors are associated with successfully recruiting close friends.

## Methods

### Study Design

This study uses a 2-group randomized trial design to test the effectiveness of reimbursements for peer referral in a web-based cross-sectional peer network survey. Participants will either be randomized to scaled group reimbursement (the experimental group) or fixed individual reimbursement groups (the control group). The trial will be of 60 days duration. Figure 1 illustrates the study design.

**Figure 1 figure1:**
[figure not shown]
Study design.

### Participants and Eligibility

This trial involves both primary participants and secondary participants. Primary participants are defined as individuals recruited through the recruitment platforms (Instagram, Snapchat, and the Student Edge panel) and are able to refer their close friends. Secondary participants are individuals nominated by a close friend and referred to the study by a primary participant.

Primary participants will be eligible if they are aged between16 and 18 years and are currently living in Australia. Secondary participants will be eligible if they are aged 16 years or older and currently living in Australia.

### Intervention

All primary and secondary participants will receive Aus $5 (US $3.70) as reimbursement for their own survey completion. Primary participants will be randomized to either (1) scaled group reimbursement (experimental) or (2) fixed individual reimbursement (control). In the scaled group reimbursement, all participants within a peer network (ie, the primary participant and all secondary participants) will receive an additional Aus $5 (US $3.70) voucher for each added secondary participant that the primary participant recruits to the study, up to a maximum total value of Aus $30 (US $22.20) per participant. The reimbursement per participant stops increasing at 6 per peer group, but up to 11 people in a peer group can be referred and reimbursed up to Aus $30 (US $22.20) each (1 primary and 10 secondary). In the fixed individual reimbursement, all participants will only be reimbursed Aus $5 (US $3.70) for their own survey completion. Table 1 describes the reimbursement amounts for participants in each group depending on the number of secondary participants who complete the survey within their friendship group.

**Table 1 table1:** Reimbursements for each intervention group.

Number of participants in friend group who complete survey	Reimbursement value per participant	
	Scaled group reimbursement (experimental)	Fixed individual reimbursement (control)
1 primary; 0 secondary	Aus $5 (US $3.70)	Aus $5 (US $3.70)
1 primary; 1 secondary	Aus $10 (US $7.40)	Aus $5 (US $3.70)
1 primary; 2 secondary	Aus $15 (US $11.10)	Aus $5 (US $3.70)
1 primary; 3 secondary	Aus $20 (US $14.80)	Aus $5 (US $3.70)
1 primary; 4 secondary	Aus $25 (US $18.50)	Aus $5 (US $3.70)
1 primary; 5-10 secondary	Aus $30 (US $22.20)	Aus $5 (US $3.70)

Reimbursements are in the form of a gift voucher sent by SMS to participants’ mobile numbers using a third-party service provider at the end of the trial period. However, due to the procedures of Student Edge, primary participants recruited through this setting will receive the initial Aus $5 (US $3.70) reimbursement on survey completion through Student Edge and further reimbursements via SMS at the end of the study, if applicable.

### Outcomes

The primary outcome is defined as the proportion of primary participants’ close friends who complete the survey. Survey completion is recorded if the secondary participant clicks the final survey submission button. This outcome measure indicates the level of complete data about each primary participant’s close friend network.

The secondary outcome is the number of close friends who complete the survey per primary participant. This outcome measure assesses whether the reimbursement model results in an overall higher number of participants.

### Sample Size

We calculated the required sample size to test the difference in proportion of an individual’s close friend network that completes the survey between the intervention and control groups. Based on previous literature, we estimated that the average number of close friends listed in the survey (nominations) is expected to be 3 [9,11,25], and that approximately half of the primary participants in the scaled reimbursement group would successfully recruit at least one friend into the study [22,23]. Based on these data and assuming that the probability of recruiting each friend is binomial, with the probability of recruiting no friends being (1–*p*)^*n*, where *n* is the total number of friends and *p* is the probability of each friend being recruited, we estimated that the probability of any one nomination being recruited would be 0.2. We assessed the sample size required for 80% power to detect a 2-fold difference in proportion between the scaled group reimbursement and fixed individual reimbursement groups. We assumed some variation between friendship groups and considered each friendship group as a cluster, with an assumed intracluster correlation (ICC) of 0.5 and a mean cluster size of 3, with a coefficient of variation for cluster size of 0.83. Based on these assumptions, 153 primary participants must be randomized to each group, and a total sample of 306 primary participants is required. Based on this sample size, we will also be able to detect a difference in the number of close friends per participant who complete the survey of 1.4 and 80% power. In total, across both groups, we estimate that at least 92 secondary participants will be recruited based on conservative assumptions.

Since we plan to recruit through 3 primary participant recruitment settings, we intend to recruit 102 primary participants from each setting (Instagram, Snapchat, and the Student Edge panel). Recruitment in each setting will continue until 102 primary participants are reached, or 6 weeks have passed. If fewer than 102 participants are recruited from any setting, further recruitment will be conducted from successful settings.

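### The stated 80%-power difference of 1.4 completed friends per participant does not follow from the plan's inputs, which give about 0.36, and power for the anticipated difference of 0.3 is about 64%

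*Protocol article*

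**What the plan says.** The Sample Size section builds the trial size on the proportion outcome. It assumes that "the average number of close friends listed in the survey (nominations) is expected to be 3" and that "approximately half of the primary participants in the scaled reimbursement group would successfully recruit at least one friend", from which "we estimated that the probability of any one nomination being recruited would be 0.2". The target is "80% power to detect a 2-fold difference in proportion between the scaled group reimbursement and fixed individual reimbursement groups", with "an assumed intracluster correlation (ICC) of 0.5 and a mean cluster size of 3" and a coefficient of variation (CV) of cluster size of 0.83. This gives 153 primary participants per group, 306 in all.

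The section then adds that the same sample can "detect a difference in the number of close friends per participant who complete the survey of 1.4 and 80% power". It gives no SD, dispersion, control mean, alpha or method for that figure. It closes by expecting at least 92 secondary participants across both groups.

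The count outcome answers the second research question under the primary aim, whether scaled reimbursement will "increase the number of close friends per participant who complete the survey compared to having no peer referral reimbursement". It is the only outcome that the Outcomes section names as secondary. Data Collection limits the count to between 0 and 10. Statistical Analysis leaves the count distribution to be chosen to suit the data.

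**The concern.** The 1.4 sits in the same paragraph as inputs with which it does not fit. Three nominations at recruitment probabilities of 0.2 and 0.1 mean 0.6 and 0.3 completed friends per primary participant. A difference of 1.4 is more than twice the whole mean expected in the scaled group. From a control mean of 0.3 it would need 1.7 of 3 friends recruited (57%, against the 20% assumed).

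At stake is how the count result is read. The sentence presents the second research question as covered by the sample size, but power at 1.4 says nothing about power at the effect the plan expects. If that power is well under 80%, a non-significant count result is weak evidence of no effect, and readers should know this before the results appear.

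**Working it through.** **Inputs (Sample Size unless noted).** Mean network size m = 3; CV 0.83, so the SD of network size is 3 × 0.83 = 2.49, its variance 6.20 and E(m²) = 9 + 6.20 = 15.20. Recruitment probability 0.2 (scaled) and, from the 2-fold difference, 0.1 (control). ICC 0.5. 153 per group. Range 0 to 10 (Data Collection). Alpha is not stated; two-sided 0.05 is assumed, so z = 1.960 + 0.842 = 2.80.

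**1. The plan's 153 reproduces.** Two proportions, 0.2 against 0.1, need 199 friends per group without clustering. The design effect for unequal clusters is [1 + (m − 1)ICC] / [1 − CV² L(1 − L)] with L = m / (m + (1 − ICC)/ICC) = 0.75. That is 2.0/0.871 = 2.297. Then 199 × 2.297 / 3 = 152.3, rounded up to 153.

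This does not settle alpha. One-sided 0.05, probabilities 0.206 and 0.103, and the simpler design effect 1 + [(1 + CV²)m − 1]ICC = 3.03 give 151 × 3.03 / 3, about 152.7, which also rounds to 153. One-sided results are therefore given below as well.

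**2. The SD that 1.4 requires.** Detectable difference = SD × 2.80 × √(2/153), so SD = 1.4 / (2.80 × 0.1143) = 4.37. One-sided (z = 2.49) it would be 4.92.

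**3. The largest SD the inputs allow.** Completed friends cannot exceed nominated friends, so the SD cannot exceed √E(m²) = √15.20 = 3.90, whatever the recruitment probability or ICC. The detectable difference therefore cannot exceed 3.90 × 2.80 × 0.1143 = 1.25. Using only the 0 to 10 range, with means of 1.7 and 0.3 (the situation in which 1.4 is true), the SD ceilings are √(1.7 × 8.3) = 3.76 and √(0.3 × 9.7) = 1.71. The ceiling on the detectable difference is then 2.80 × √((14.11 + 2.91)/153) = 0.93.

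**4. The SD the inputs imply.** With the ICC read as a beta-binomial correlation, Var = p(1 − p)[E(m) + ICC(E(m²) − E(m))] + p² Var(m).
- Scaled: 0.16 × (3 + 0.5 × 12.20) + 0.04 × 6.20 = 1.70, SD 1.31.
- Control: 0.09 × 9.10 + 0.01 × 6.20 = 0.88, SD 0.94.
- Standard error of the difference: √(2.585/153) = 0.130.
- Detectable difference: 2.80 × 0.130 = 0.36 (one-sided 0.32).
- Power at 0.3: Φ(0.3/0.130 − 1.96) = 64%. Simulation gave 63% to 65%. One-sided, Φ(0.3/0.130 − 1.645) is about 75%.
- For 80% power at 0.3, about 226 per group would be needed.

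**5. Sensitivity (two-sided 0.05, 153 per group).**

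| Assumption | Detectable difference | Power at 0.3 |
|---|---|---|
| ICC 0.5, CV 0.83 (plan) | 0.36 | 64% |
| ICC 0.5, every network exactly 3 | 0.28 | 86% |
| ICC 1, CV 0.83 | 0.46 | 45% |
| ICC 0, CV 0.83 | 0.23 | 95% |
| ICC 0, every network exactly 3 | 0.20 | 99% |

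In every row, power at a difference of 1.4 is above 99.9%.

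**6. Could 1.4 be a rate ratio?** With a control mean of 0.3, a ratio of 1.4 has 41% power under a plain Poisson model. The 80%-power ratio is about 1.69, rising to 2.04 with a variance inflation of 2 and 2.36 with 3.03. So no.

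**7. Scale against the expected totals.** The planned rates give 153 × 0.6 + 153 × 0.3, about 138 secondary participants. The stated minimum of 92 matches 306 × 0.3 = 91.8. A difference of 1.4 would mean 153 × 1.4, about 214 more in the scaled group than in control.

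**The case against.** Several points on the other side stand.

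- **0.3 is not the correct replacement for 1.4.** A reader might infer that the detectable difference should have been 0.3. That is the anticipated effect; a detectable difference depends on the SD and sample size, and a detectable difference larger than the anticipated one is not in itself an arithmetic error. The comparable figure is about 0.36.
- **The sentence does not overclaim power at 1.4.** A reader might infer that 153 per group is too few to detect 1.4. The opposite holds: power there is essentially 100%, so the sentence understates the test's sensitivity. Nor does the document state any power for 0.3.
- **A possible origin exists.** Using the SD of nominations (2.49) and a design effect of 3.03 on 153 gives 2.80 × 2.49 × √(2 × 3.03/153) = 1.39. To say that 1.4 cannot be connected with the stated inputs at all would therefore go too far. But the route is not valid: it uses the spread of nominations instead of completions and applies a friend-level design effect to a participant-level count. With the design effect of 2.30 it gives 1.21, and with 3.03 and one-sided alpha 1.23.
- **The article is condensed.** A separate SD could stand in a full protocol. However, the SD needed exceeds the ceiling set by the mean network size and CV that the article itself gives.
- **The 0.36 and 64% rest on assumptions.** They need an unstated alpha, a beta-binomial reading of the ICC and a count model that is left open. Adjusting for network size moved simulated power to 68% at ICC 0.5 and 82% at ICC 0.3. The premise that half of the scaled group recruit at least one friend was itself worked through as independent recruitment of each friend, which is nearer ICC 0.

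The harm should also not be exaggerated. The count result will presumably be read from its estimate and confidence interval, and nothing in the article says that 1.4 will be treated as an effect ruled out.

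**Conclusion.** The concern holds in a limited form. The 1.4 is a wrong stated figure: it needs an SD of 4.37 where the plan's inputs allow at most 3.90 and imply about 1.31 and 0.94. It is about 3.8 times the detectable difference that those inputs give (0.36) and about 4.7 times the difference that they anticipate (0.3), so it offers no assurance for the second research question. Under the plan's own ICC and CV, with two-sided alpha 0.05, the count outcome has about 64% power for the expected effect, so a true doubling would be missed roughly one time in three. That power falls below 80% under either alpha reading at ICC 0.5 and CV 0.83, but it would exceed 80% with equal networks of 3 or a much lower ICC.

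A reader might go further and conclude that the trial is undersized. The documents do not support that: 153 per group reproduces for the primary outcome, and the defect is confined to one sentence about a secondary outcome. It should be fixed, at moderate priority.

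**What to change.** Replace the sentence with a recomputed detectable difference that states its SD or dispersion, control mean and alpha. A version to adapt, once the authors confirm alpha and how the ICC is to be read: *With 153 primary participants per group, control mean 0.3, SDs of about 1.31 and 0.94 (ICC 0.5, CV of network size 0.83) and two-sided alpha 0.05, the difference in completed friends per participant detectable with 80% power is about 0.36 (0.20 to 0.46 over ICC 0 to 1, the lower end with every network exactly 3). Power for the anticipated difference of 0.3 is about 64% (about 45% at ICC 1; about 86% if every network is exactly 3).*

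Add that, under these assumptions, the count outcome is not powered at 80% for the expected effect. If the authors have a different SD or method for 1.4, they should state it and reconcile it with the mean network size, CV and range in the article.

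The cost is one or two sentences. No participants, design features or primary analysis change. The Results section says that analysis had not commenced, so the correction can be recorded before results are known.
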